**Fig 1 pone.0306053.g001:**
[figure not shown]
Overall study design represents the study’s flow from enrollment through various interventions to the endpoints over 24 months.

### Recruitment

A member of the research team will search the University of Chicago operating room schedules of the surgeons to identify potential study participants scheduled to undergo a myomectomy. Data from the medical record system will be used to evaluate inclusion criteria. Patients presenting to the clinic for a consultation for fibroid symptoms or fibroid management (after clinical confirmation of their eligibility for admission into the study based on inclusion & exclusion criteria) will also be considered.

Once a potential participant is identified, they will be approached to participate by a member of the research team. Contact is established via MyChart, email, phone number, in person at the clinic, or pre-op. Eligibility criteria will be confirmed by reviewing medical history and thorough discussion with potential subjects. If eligibility is confirmed, the potential subject will be offered participation in the study. At this time, study details will be explained. Risks and benefits will be thoroughly discussed, and consent given to the participant.

### Inclusion criteria

Has voluntarily signed and dated the informed consent form prior to initiation of any screening or study-specific proceduresPremenopausal female aged 18 years and older on the day of signing of the informed consent formHas a diagnosis of uterine fibroids that is confirmed by a pelvic ultrasound (transvaginal and/or transabdominal) performed during the screening period.Has at least one or more of the following symptoms:Moderate to heavy menses defined as PBAC score ≥ 120.Pelvic pain during menses measured on NRS ≥ 4 at baseline.Moderately severe fibroid-related symptoms (a score ≥ 25 on the UF quality of life symptoms severity subscale)Has a negative urine pregnancy test at the Screening, Baseline and interval clinic visitsAgrees to not be pregnant for at least 12 months. Participants may use any form of non-hormonal contraception consistently during the screening period and the randomized treatment period. These may include Diaphragm, cervical cap, spermicides, male and female condoms, copper IUD and sponge.Has an endometrial (aspiration) biopsy, if clinically indicated, performed during the screening period, with results showing no clinically significant endometrial pathology (hyperplasia, endometritis, or endometrial cancer).

### Exclusion criteria

Has transvaginal and/or transabdominal ultrasound during the screening period demonstrating pathology other than uterine fibroids that could be responsible for or contributing to the patient’s heavy menstrual bleeding, such as uterine or cervical polyps > 2.0 cm, or any other clinically significant gynecological disorder determined by the investigator to require further evaluation and/or treatment.Has unexplained vaginal bleeding outside of the patient’s regular menstrual cycleHas undergone ultrasound-guided laparoscopic radiofrequency ablation, or any other surgical procedure for fibroids, uterine artery embolization, magnetic resonance-guided focused ultrasound for fibroids, as well as endometrial ablation for abnormal uterine bleeding within 6 months prior to the Screening visitHas a history of or currently has osteoporosis, or other metabolic bone disease, hyperparathyroidism, hyperprolactinemia, hyperthyroidism, anorexia nervosa, or low traumatic (from the standing position) or atraumatic fracture (toe, finger, skull, face, and ankle fractures are allowed). A history of successfully treated hyperparathyroidism, hyperprolactinemia, or hyperthyroidism is allowed if the patient’s bone mineral density is within normal limits.Has a history of the use of bisphosphonates, calcitonin, calcitriol, ipriflavone, teriparatide, denosumab, or any medication other than calcium and vitamin D preparations to treat bone mineral density lossAnticipated use of systemic glucocorticoids at an oral prednisone-equivalent dose of more than 5 mg every other day during the study. Note: topical, inhaled, intranasal, optic, ophthalmic, intraarticular, or intralesional subcutaneous are permitted without restrictionGastrointestinal disorder affecting absorption or gastrointestinal motilityHas any additional contraindication to treatment with low-dose estradiol and norethindrone acetate, including:Current, known, suspected, or history of breast cancer.Current, known, or suspected hormone-dependent neoplasiaHigh risk of arterial, venous thrombotic disorder or thromboembolic disorder, i.e. women over 35 years of age who smoke or women with uncontrolled hypertension.Known anaphylactic reaction or angioedema or hypersensitivity to estradiol or norethindrone acetate.Currently pregnant or lactating or intends to become pregnant or to donate ova during the study period or within 1 month after the end of the study.Active thrombotic or thromboembolic disease or history of these conditions prior to the Baseline Day 1 visit or risk factors for such conditions. These conditions include:deep vein thrombosispulmonary embolismvascular disease (e.g., cerebrovascular disease, coronary artery disease, peripheral vascular disease)inherited or acquired hypercoagulopathies, known protein C, protein S, or antithrombin deficiency, or other known thrombophilia disorders, including Factor V Leiden thrombogenic valvular or thrombogenic rhythm diseases of the heart (for example, subacute bacterial endocarditis with valvular disease, or atrial fibrillation)uncontrolled hypertensionheadaches with focal neurological symptoms or migraine headaches with aura if over 35 years of ageWomen at increased risk for thrombotic or thromboembolic eventsHas jaundice or known current active liver disease from any cause, including hepatitis A (HAV IgM), hepatitis B (HBsAg), or hepatitis C (HCV Ab positive, confirmed by HCV RNA)Has any of the following cervical pathology: high-grade cervical neoplasia, atypical glandular cells, atypical endocervical cells, atypical squamous cells favoring high grade. Of note, patients with atypical squamous cells of undetermined significance and low-grade cervical neoplasia may be included in the study if high-risk human papillomavirus testing is negative or if DNA testing for human papillomavirus 16 and 18 DNA testing is negative.Has any history of clinical laboratory abnormalities indicating hepatic or gallbladder impairment.Has clinically significant cardiovascular disease including:Prior history of myocardial infarctionHistory of anginaHistory of congestive heart failureHistory of clinically significant ventricular arrhythmias such as ventricular tachycardia, ventricular fibrillation, or torsade de pointes, or Mobitz II second-degree or third-degree heart block without a permanent pacemaker in place or untreated supraventricular tachycardia (heart rate ≥ 120 beats per minute)QT interval by the Fridericia correction formula (QTcF) of > 470 msecHypotension, as indicated by systolic blood pressure < 84 millimeters of mercury (mmHg) on 2 repeat measures at least 15 minutes apart or treated ongoing symptomatic orthostatic hypotension with > 20 mmHg decrease in systolic blood pressure one minute or more after assuming an upright position.Uncontrolled hypertension, as indicated by systolic blood pressure > 160 mmHg on 2 repeat measures at least 15 minutes apart or diastolic blood pressure > 100 mmHg at any screening visit or the Baseline Day 1 visit.Bradycardia as indicated by a heart rate of < 45 beats per minute on the screening electrocardiogram.Has been a participant in an investigational drug or device study within the 1 month prior to the screening visit.Has a history of clinically significant condition(s) including, but not limited to:Untreated thyroid dysfunction or palpable thyroid abnormality (patients with adequately treated hypothyroidism who are stable on medication are not excluded).History of malignancy within the past 5 years or ongoing malignancy other than curatively treated nonmelanoma skin cancer or surgically cured Stage 0 in situ melanomaAny current psychiatric disorder that would, in the opinion of the investigator or medical monitor, impair the ability of the patient to participate in the study or would impair the interpretation of their data.Has a prior (within 1 year of Screening 1 visit) or current history of drug or alcohol abuse disorder according to Diagnostic and Statistical Manual of Mental Disorders V (all patients must be questioned about their drug and alcohol use, and this should be documented in the electronic case report form)Has participated in a previous clinical study that included the use of Relugolix or has received this treatment within 3 months of the study.Is inappropriate for participation in this study for other reasons, as determined by the investigator, sub-investigator, or medical monitor.

### Randomization

Randomization will be prepared by the study statistician using computer-generated random numbers and the method of permuted blocks. It will be implemented using the REDCap randomization module with varying blocks of size 4, 6, and 8 (in a random order) [14]. No one other than the statistician will have access to the sequence of block sizes. Eligible patients will be assigned to one of the following arms:

Arm 1: Treatment with Relugolix combination therapy (Myfembree®) after surgical myomectomy.Arm 2: Treatment with standard of care (SoC) after surgical myomectomy.

### Variables

The primary outcome will be a composite outcome including:

Fibroid recurrence when compared to the post-myomectomy baseline pelvic ultrasound (transvaginal and/or transabdominal), defined as a new fibroid identified on ultrasound with volume >1 cm3 [8]Symptom recurrence defined as either of the following:I. Moderate to heavy menses with PBAC score ≥ 120 for patients with pre-operative heavy mensesII. Pelvic pain during menses as measured on the Numerical Rating Scale NRS ≥ 4 at baselineIII. Score ≥ 25 on the symptom severity scale.Need for reintervention defined as need to undergo a procedure or surgery for treatment of uterine fibroids including repeat myomectomy, uterine fibroid embolization, radiofrequency ablation or hysterectomy.

The secondary outcomes will include:

Fibroid recurrence, compared to baseline pelvic ultrasound (transvaginal and/or transabdominal), defined as a new fibroid identified on ultrasound with volume >1 cm3.Return of moderate to heavy menses defined as PBAC score ≥ 120 for patients with pre-operative moderate to heavy menses.Need for reintervention defined as need to undergo a procedure or surgery for treatment of uterine fibroids including repeat myomectomy, uterine fibroid embolization, and radiofrequency ablation.Time to event (procedure or surgery) such as radiofrequency ablation (RFA), myomectomy, hysterectomy, or uterine fibroid embolization (UFE).Symptom recurrence according to the UF quality of life symptoms severity subscale and Bleeding & pelvic discomfort (BPD) scale.Return of pelvic pain during menses as measured on NRS [15]Quality of life as measured by Patient Reported Outcome and Quality of life questionnaires (UFS-QOL, WPAI:SHP, Female Sexual Function Index)

### Intervention

At 4–6 weeks post-surgery, participants will complete a baseline ultrasound. Participants in the medication arm will receive a once-daily pill that contains Relugolix (a gonadotropin-releasing hormone antagonist), estradiol (an estrogen), and norethindrone acetate (a progestin). Myfembree will be dispensed after randomization at study visit 1. Pill counts and checks will be completed at each visit. A total of 10 visits are necessary including the screening visit.

All participants will be asked to fill out questionnaires at baseline and then every 3 months. The questionnaires will be filled by paper or electronically using uMotif e-diary.

Uterine Fibroid Symptom and Health-Related Quality of Life (UFS-QoL) fibroid QuestionnaireWork Productivity and Activity Impairment Questionnaire: Specific Health Problem V2.0 (WPAI:SHP)Female Sexual Function Index (FSFI)

All participants will be asked to fill a set of diaries at baseline and daily for the study duration.

Daily electronic diaries (eDiary) to measure compliance with study treatmentMenstrual bleeding diaryRecord of use of feminine products for menstrual bleedingPictorial bleeding assessment chart (PBAC) scoresPelvic pain during menses by the numeric rating scale (NRS)Use of pain medication to treat pain caused by uterine fibroids

Participants will have access to all questionnaires once they are enrolled in the study and they will be accessible anywhere through their phones, mobile, or computer devices.

All participants will undergo pelvic ultrasounds at the following time periods:

Week 4–6: post-myomectomy baseline ultrasound (transvaginal and/or transabdominal)Month 6: pelvic ultrasound (transvaginal and/or transabdominal)Month 12: pelvic ultrasound (transvaginal and/or transabdominal)Month 18: pelvic ultrasound (transvaginal and/or transabdominal)Month 24: pelvic ultrasound (transvaginal and/or transabdominal)

All participants will have blood work performed every 6 months or at clinically indicated intervals:

Cell Blood Count (CBC)Complete Metabolic Panel (CMP)Urine pregnancy test during each clinic/in-person visit.

Please refer to Fig 2 for a detailed study timeline & interventions.

**Fig 2 pone.0306053.g002:**
[figure not shown]
Timeline and Interventions Illustrate the structured timeline and intervention schematic for a 24-month clinical study, detailing enrollment, interventions, and assessments including UFS-QOL and pelvic ultrasounds at specified time points.

### Sample size and statistical analysis

Data analysis and statistical support is obtained through the Biostatistics Laboratory (located within the Department of Public Health Sciences) at the University of Chicago. The primary endpoint of this study will be a composite endpoint defined as the occurrence of any of the following three component endpoints over a 24 month follow up period.

Endpoint 1 (Fibroid Recurrence)

Endpoint 2 (Symptom Recurrence)

Endpoint 3 (Need for Re-intervention)

A Chi-square test will be used to compare the rate of occurrence of the primary endpoint in the two treatment arms.

Assumptions regarding the frequency of endpoint 1 are based on ref [8]. That study observed 23% recurrences in the abdominal group and 27% in the laparoscopic group over 40 months. 84% of these recurrences were seen within 24 months. Therefore, we assume the recurrence rate among patients with laparoscopic or abdominal surgery over 24-month follow-up time in the control arm will be (23%+27%)/2*0.84 = 21%. We assume a recurrence rate of 5% in the treatment group (i.e., effect size of 16% absolute reduction). For endpoint 2, a symptom recurrence rate of 7.6% in the control group [16], and 1.5% in the treatment group are assumed. For endpoint 3, a reintervention rate of 14.4% [16] in the control group and 3% in the treatment group are assumed. Assuming endpoint 1 is independent of endpoints 2 and 3, and a correlation of 0.5 between the endpoints 2 and 3, leads to a rate of 33.8% for our primary composite endpoint in the control arm vs. 8.25% in the treatment group. A sample size of 94 patients (47 per arm) will provide 80% power to detect a difference of this magnitude at a two-sided alpha level of 0.05 (PASS, Kaysville, Utah) utilizing the chi-square test as the statistical testing method. To allow for a 30% dropout rate, the sample size will be increased to 136 patients. It is expected that the 136 patients will be accrued during the first year of the trial (10–12 per month) with two years of follow-up after the last patient is enrolled. The number needed to treat (NNT) will be calculated as the reciprocal of the difference in observed event rates along with a 95% confidence interval. While the sample size has been increased to allow for a 30% dropout rate, every effort will be made to retain subjects in the trial and to obtain outcome data. Sensitivity analyses will be performed to examine the effects of dropouts on the results.

As secondary endpoints, we will analyze the three components of the primary endpoint (recurrence, symptoms, and re-intervention) separately using Chi-square or Fisher’s exact tests. Adverse event (AE) rates will be summarized by type, grade, and attribution and monitored periodically by the investigative team and compared between groups using Chi-square or Fisher’s exact tests. All categorical data will be summarized as frequencies and percentages. Pain scores and quality of life (QOL) measures over time will be summarized as means and standard deviations or medians and interquartile ranges depending on the shape of the distribution. Comparisons between groups will be performed using mixed effects models for longitudinal data [14]. Empirical semi-variograms will be constructed to assess the underlying covariance structure together with information criteria (AIC). If a suitable parametric form (for example, AR(1)) cannot be identified we will utilize an unstructured variance-covariance structure. Finally, Kaplan-Meier curves will be generated for time-to-event outcomes; logrank tests will be performed for group comparisons. REDCap will be used for data capture and data management while SAS (Raleigh, NC) and STATA (College Station, TX) will be the principal software employed for data analysis.

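### Optional gain on the secondary components: where Fisher's exact test would be used, Boschloo's exact test is less conservative and adds power for symptoms and reintervention

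*Protocol article*

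**What the plan says.** Under the heading Sample size and statistical analysis, the protocol article names the tests for the components: "we will analyze the three components of the primary endpoint (recurrence, symptoms, and re-intervention) separately using Chi-square or Fisher’s exact tests". It does not say when each test applies, and it states no power for any component.

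The same section supplies the figures needed to judge the choice:

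- Level, stated for the primary test: "at a two-sided alpha level of 0.05".
- Evaluable patients: "A sample size of 94 patients (47 per arm) will provide 80% power", raised to 136 enrolled (68 per arm) for 30% dropout.
- Symptoms: "a symptom recurrence rate of 7.6% in the control group [16], and 1.5% in the treatment group are assumed".
- Reintervention: "a reintervention rate of 14.4% [16] in the control group and 3% in the treatment group are assumed".

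**The concern.** On the plan's own rates, symptoms and reintervention are rare enough that Fisher's test is the likely choice at 47 per arm. Fisher conditions on the total number of events. With few events the attainable p-values are coarse, and the true type I error falls well below 5%. That unused error is lost power.

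The composite mixes an ultrasound finding with symptoms and procedures. The separate component tests help to show whether a benefit goes beyond the ultrasound finding, so power given away there, without any protection beyond the nominal 5%, is worth recovering if the cost is small.

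**Working it through.** **1. The plan's own figures.** Apply the stated assumption, "Assuming endpoint 1 is independent of endpoints 2 and 3, and a correlation of 0.5 between the endpoints 2 and 3".

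- Control, endpoints 2 and 3 together: 0.076 × 0.144 + 0.5 × √(0.076 × 0.924 × 0.144 × 0.856) = 0.0575. Either one: 0.076 + 0.144 − 0.0575 = 0.1625. Composite: 1 − (1 − 0.1625)(1 − 0.21) = 33.8%.
- Treatment, the same way: joint 0.0108, either 0.0342, composite 1 − (1 − 0.0342)(1 − 0.05) = 8.25%.

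These match "33.8% for our primary composite endpoint in the control arm vs. 8.25% in the treatment group". The usual two-proportion formula with continuity correction then gives 47 per arm, as stated (39 without the correction). For dropout, 47/0.7 = 67.1, so 68 per arm and 136 in total. The inputs are therefore read as the plan intends.

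**2. Expected events per arm** (n × mean of the two rates).

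| | 47 per arm | 68 per arm |
|---|---|---|
| Reintervention, mean rate (14.4% + 3%)/2 = 8.7% | 4.1 | 5.9 |
| Symptoms, mean rate (7.6% + 1.5%)/2 = 4.55% | 2.1 | 3.1 |

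The customary rule is an assumption here; the article does not state it. It is applied to the observed margins. With equal arms the smallest expected count is half the total events, so the exact test applies when there are 9 events or fewer in total. At the plan's rates this happens in 70% of trials for reintervention and 99% for symptoms at 47 per arm, and in 24% and 91% at 68.

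**3. Method.** All 2×2 tables (x₁, x₂) were enumerated under two independent binomials:

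P(reject) = Σ over rejected tables of Bin(x₁; n, p₁) × Bin(x₂; n, p₂).

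Setting p₁ and p₂ to the plan's rates gives power; setting p₁ = p₂ gives true size. Fisher rejects at two-sided p ≤ 0.05. Boschloo rejects when the Fisher p-value is at or below the largest cut-off whose maximum size over a fine grid of common rates is at most 5%. That cut-off is 0.076 at 47 per arm and 0.071 at 68.

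**4. True size at 47 per arm.**

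| Test | At 8.7% | At 4.55% | Maximum over all rates |
|---|---|---|---|
| Fisher | 1.5% | 0.5% | 3.1% |
| Boschloo | 3.2% | 1.7% | 4.95% |
| Uncorrected chi-square | 6.1% | 4.7% | 6.1% |

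**5. Power and maximum size.**

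| Rule | Reintervention, 47 / 68 | Symptoms, 47 / 68 | Maximum size, 47 / 68 |
|---|---|---|---|
| Fisher always | 33.1% / 56.2% | 8.0% / 20.8% | 3.1% / 3.4% |
| Boschloo always | 45.2% / 63.9% | 16.3% / 32.3% | 4.95% / 4.93% |
| Chi-square, else Fisher | 39.8% / 67.0% | 8.2% / 23.1% | 5.29% / 5.20% |
| Chi-square, else Boschloo | 48.7% / 70.0% | 16.5% / 33.8% | 5.37% / 5.20% |

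The last two rows are the like-for-like comparison. They differ only in the exact test used when counts are small.

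**6. What changes in practice.** At 47 per arm, 5 vs 0 events (Fisher p = 0.056) and 7 vs 1 events (p = 0.059) both fall in the exact-test branch. Neither is significant by Fisher at 5%; both are by Boschloo.

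**The case against.** The strongest reply is that nothing here is wrong. Chi-square or Fisher is a conventional and valid choice for secondary endpoints, and the rule for choosing between them may well sit in an analysis plan that is not shown. That stands: neither the naming of Fisher nor the lack of a switching rule is an error.

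A reader might infer that the plan's power for reintervention is 33% and would become 45%. The documents do not support that. The article allows chi-square as well as Fisher, so 33% applies only if Fisher is always used. Under the customary rule the comparison at 47 per arm is 40% with 49%. At 68 per arm the existing pair of tests already gives 67%, more than Boschloo used throughout (64%).

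A reader might also infer that the swap guarantees 5%. Boschloo used throughout does so; the mixed rule does not (5.37% and 5.20%). But the mixed rule with Fisher does not either (5.29% and 5.20%), so the swap costs almost nothing in level.

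Three further limits stand. Power remains low, so a non-significant component result would still say little. The article also plans logrank tests for time-to-event outcomes and lists time to procedure or surgery as a secondary outcome, so reintervention does not rest on this test alone. And no gain was computed for adverse events, for which the article names the same tests.

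**Conclusion.** The point holds as an optional efficiency gain on secondary endpoints. Replacing Fisher by Boschloo where Fisher would be used adds about 9 percentage points for reintervention (39.8% to 48.7%) and about 8 for symptoms (8.2% to 16.5%) at 47 per arm. At 68 per arm it adds about 3 (67.0% to 70.0%) and about 11 (23.1% to 33.8%).

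This rests on the plan's assumed rates, on a two-sided 5% level for the component tests (the article states it only for the primary test), on equal arms of 47 or 68 evaluable patients, and on the customary expected-count rule. It does not show that the plan is invalid, that the primary analysis is affected, or that the components become adequately powered.

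**What to change.** In the paragraph on secondary endpoints, name Boschloo's exact test in place of Fisher's for the three components, and state the choice before the data are seen. Either version is defensible:

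- **Mixed rule:** chi-square if all expected counts are at least 5, otherwise Boschloo. This has the higher power of the two versions, with a maximum size of about 5.4% at 47 per arm and 5.2% at 68.
- **Boschloo throughout:** strict 5% guarantee (maximum size 4.95% and 4.93%), with reintervention power of 45% and 64% and symptom power of 16% and 32%.

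Uncorrected chi-square throughout is not a safe way to gain power at 47 per arm, since its size reaches 6.1% near the pooled reintervention rate. For adverse events the present wording can stay unless the gain is worked out there too.

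The cost is a change of wording and somewhat less familiar software. No data, visits or patients are added.
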